## Abstract

**Background:**

Pneumonia is responsible for a large proportion of hospital admissions and antibiotic utilization. Physician adherence to evidence-based pneumonia management guidelines is poor. Antimicrobial stewardship programs (ASPs) are an effective intervention to mitigate against unwarranted variation from these guidelines. Despite this benefit, ASPs have not been shown to reduce the length of stay of hospitalized patients with pneumonia. In immune-competent adult patients admitted to a hospital ward with a diagnosis of community-acquired pneumonia, does a multi-faceted ASP utilizing prospective chart audit and feedback reduce the length of stay, compared with usual care, without increasing the risk of death or readmission 30 days after discharge from hospital?

**Methods/Design:**

Starting on 1 April 2013, all consecutive immune-competent adult patients (>18 years old) admitted to a hospital ward with a positive febrile respiratory illness screening questionnaire and a diagnosis of pneumonia by the attending physician will be eligible for inclusion in this non-randomized study. All eligible patients who fulfill the ASP review criteria will undergo a prospective chart audit, followed by an ASP recommendation provided to the attending physician. The attending physician is responsible for implementing or rejecting the ASP recommendation. This is a modified stepped-wedge design with a baseline data collection period of 3 months, followed by non-random sequential introduction of the ASP intervention on each of four hospital wards in a single community-based, academic-affiliated 339-bed acute-care hospital in Barrie, ON, Canada. The primary outcome measure is hospital length of stay; secondary outcome measures include days and duration of antibiotic therapy, and inadvertent adverse outcomes of 30 day post-discharge mortality and hospital readmission rates. Differences in outcome measures will be assessed using extended Cox regression analysis. Time to ASP intervention is included as a time-dependent covariate in the final model, to account for time-dependent bias.

**Discussion:**

By designing a pragmatic clinical trial with unique design and analytic features, we not only expect to demonstrate the effectiveness of a real-world ASP, but also provide a model for program evaluation that can be used more broadly to improve patient safety and quality of care.

**Trial registration:**

ClinicalTrials.gov NCT02264756.

## Background

### Community-acquired pneumonia

Community-acquired pneumonia (CAP) is defined as an acute infection of the lower respiratory tract in patients residing outside of hospital for 90 days or longer before presentation [1]. Residents of long-term care homes or nursing homes are frequently diagnosed as having a microbiologically variant form of CAP, but there is little evidence to support this classification system [2, 3]. There is no gold-standard diagnostic test or set of criteria for CAP [4], so the diagnosis is made clinically using a constellation of clinical signs and symptoms and diagnostic tests.

In Ontario, pneumonia is the leading cause of death from bacterial infections and accounts for over 18,000 years of life lost annually owing to premature mortality [5]. Pneumonia accounts for the majority of antibiotic utilization in both hospital and outpatient settings [6, 7]. Evidence-based guidelines for the diagnosis and management of pneumonia are available to physicians [1, 8–12]. Adherence to these evidence-based guidelines is associated with reductions in both mortality and antibiotic utilization [13–18].

### Antimicrobial stewardship

Antimicrobial stewardship is defined as any intervention that minimizes unwarranted variation in antimicrobial utilization from evidence-based best practice with the intent of improving patient safety and quality of care [19]. ‘Unwarranted’ refers to the absence of patient- or disease-specific reasons to justify practice variation from evidence-based practice standards. Antimicrobial stewardship can be operationalized in many different ways, but prospective audit and feedback (persuasive approach) and restricted antimicrobial prescribing policies (restrictive approach) appear to be the most efficacious interventions to achieve the goals of antimicrobial stewardship [19, 20]. Antimicrobial stewardship programs (ASPs) have demonstrated efficacy in improving antimicrobial prescription and reducing rates of hospital-acquired infections [20]. Antimicrobial stewardship programs directed at CAP patients have demonstrated reductions in mortality [15, 21], but have failed to demonstrate reductions in length of stay [20]. Of note, the study by Fine *et al*. [22] used a cluster randomized controlled trial design to examine the impact of an ASP on length of hospital stay in CAP patients. This was the only study to model length of stay as a time-to-event occurrence; differences between the length of stay in intervention and control groups were assessed by survival analysis. The intervention consisted of a prospective chart audit starting on day 3 of hospitalization and physician feedback in the form of a recommendation suggesting the optimal timing of conversion from intravenous to oral antibiotics. The intervention was modeled as a time-invariant dichotomous variable in the final model, despite the fact that the timing of the recommendation varied by up to 7 days from the time of enrollment. The hazard ratio for discharge was 1.16 (95 % confidence interval, 0.97–1.38) for the intervention group, suggesting a non-significant reduction in length of stay of 16 %. It is unknown whether this hazard ratio would have reached statistical significance if the intervention was modeled as a time-dependent covariate in the final model, as unaccounted-for time-dependent bias might have diluted the final intervention effect point estimate [23].

### Research question

In immune-competent adult patients admitted to a hospital ward with a diagnosis of CAP, does a multi-faceted ASP utilizing prospective chart audit and feedback reduce the length of hospital stay and days and duration of antimicrobial therapy, compared with usual care, without increasing the risk of death or readmission 30 days after discharge from hospital?

## Methods/Design

### Setting

All participants will be admitted patients of the Royal Victoria Regional Health Centre, a 339-bed community-based, university-affiliated, acute-care hospital located in Barrie, Ontario, Canada. This centre is the only hospital serving the 128,000 residents of Barrie. Access to acute medical care for Ontario residents, including all hospital services, is publicly funded by the Ministry of Health and Long-Term Care, the provincial agency responsible for funding and oversight of Ontario’s Medicare system. All patients enrolled in the study will be admitted to one of four medical wards. All study patients will be admitted to a hospitalist service. Admission to any medical ward is controlled by bed allocation, a non-medical administrative service within the hospital that is responsible for patient flow and assigning patient care. Hospitalists are not assigned to any one specific medical ward, but provide care across all medical wards.

### Population

Starting 1 April 2013, all consecutive adult patients (≥18 years old) with the following inclusion criteria will be screened for enrollment in the study [5]:Screen positive for febrile respiratory illness on admission to hospital [24], andDiagnosed with pneumonia by the admitting physician (acute exacerbations of chronic obstructive lung disease are considered within the definition of pneumonia for the purposes of this study, as they are commonly treated with the same antimicrobial regimens as patients with pneumonia), andAdmitted to a medical ward.

All patients who meet these criteria will be eligible for the intervention except for those with the following exclusion criteria [5]:Hospitalized for ≥48 consecutive hours in the preceding 3 months, orReceiving immunosuppressants (defined as ≥40 mg prednisone daily, or steroid equivalent, for ≥2 weeks preceding hospitalization or any other immunosuppressant used for systemic illness or to prevent transplant rejection), orNeutropenic (defined as a polymorphonuclear count ≤0.5 × 10^9^ cells/l) for any cause, orImmunocompromised (defined as having leukemia, lymphoma, HIV with CD4 cell count ≤200, splenectomy or receiving cytotoxic chemotherapy), orAdmitted to high-acuity units, such as intensive care units, orRequire mechanical ventilation, either non-invasive or invasive, orHave a life expectancy of ≤3 months (palliative).

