### Intervention

All eligible patients with CAP who meet the ASP review criteria will receive the ASP intervention (ASP-i). This intervention consists of a prospective chart audit and physician feedback (persuasive) approach [25]. The ASP members who conduct all the audits and make recommendations consist of a pharmacist trained in infectious diseases (LM) and a physician trained in infectious diseases (GD). All patients are reviewed by both members. The ASP-i recommendations are guided by the Infectious Diseases Society of America CAP guidelines [1] and the Canadian Thoracic Society guidelines for the management of chronic obstructive pulmonary disease [26]. The possible ASP-i recommendations are based on those recommended by the UK National Health Service [25] and include:No change to current careDiscontinue antibioticsIntravenous to oral conversionDuration of therapyDosing changeNarrow or broaden spectrum of therapy.

The ASP-i recommendations are not mutually exclusive. All recommendations are documented in the patient’s electronic medical record and communicated directly to the attending physician by the ASP members.

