### Statistical methods

An extended Cox regression analysis that models the ASP-i as a time-variant covariate will be used to compare the primary and secondary outcome measures between the control and intervention groups [34]. Violations of the proportional hazards assumption for each covariate will be identified using the method of Schoenfeld residuals combined with the graphical method of log-log survival curve analysis [34]. Results will be reported as hazard ratios with 95 % confidence intervals. Patients who remain in hospital beyond 14 days will be administratively censored. Competing events, such as death or transfer from a medical ward to a critical care unit will be assumed to be non-informative conditional on the covariates included in the final model [34]. Time to ASP-i will be modeled as a time-variant covariate in the final model to account for any time-dependent bias [23]. The ASP-i exposure will be coded as a dichotomous variable; 0 = no ASP-i, switching to 1 = ASP-i at the time of the ASP-i and remaining 1 throughout the remainder of the follow-up time. This method treats a patient who has received an ASP-i as a non-ASP-i patient prior to the intervention. Other variables known to be associated with the primary and secondary outcome measures will also be included in the final model [5], and include; age, sex, Charlson comorbidity index, CURB-65 score, time (days) to clinical resolution, and complications from pneumonia, such as empyema. Fixed effects of wards on the outcomes will accounted for by including them as indicator variables in the final model. Maturation of ASP-i effect on outcomes over time will be adjusted by including a categorical time variable in the final model (time variable will be defined as ‘quarter’ from start of study). A dichotomous variable for acceptance or rejection of the ASP-i will be part of an interaction term with the control/intervention group variable to permit a per-protocol analysis. Sensitivity analysis will be done using a competing events Cox regression model to determine the impact of the assumption of the non-informative nature of events, such as death and admission to an intensive care unit [35].

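### The primary hazard ratio covers pneumonia or COPD exacerbation but is labelled CAP, and the named model has no admission-diagnosis term

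*Protocol article*

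**What the plan says.** The Research question section sets the target population: "In immune-competent adult patients admitted to a hospital ward with a diagnosis of CAP". The Background says that CAP "is defined as an acute infection of the lower respiratory tract in patients residing outside of hospital for 90 days or longer before presentation", and does not mention COPD exacerbation there. The Recruitment section describes everyone enrolled as having CAP, the Sample size section counts CAP patients, and the Discussion states the expected benefit for CAP patients.

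The Population section is wider: "acute exacerbations of chronic obstructive lung disease are considered within the definition of pneumonia for the purposes of this study". The reason follows directly: "as they are commonly treated with the same antimicrobial regimens as patients with pneumonia". All patients must also meet this criterion: "Screen positive for febrile respiratory illness on admission to hospital". The Intervention section fits the wider population, since recommendations draw on a CAP guideline and on "the Canadian Thoracic Society guidelines for the management of chronic obstructive pulmonary disease".

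The patient-level covariates in the final Cox model are "age, sex, Charlson comorbidity index, CURB-65 score, time (days) to clinical resolution, and complications from pneumonia, such as empyema". Ward indicators and calendar quarter are added. The one named interaction concerns acceptance of the recommendation, and the one named sensitivity analysis concerns competing events. Admission diagnosis appears in none of these, and the limitations in the Discussion do not mention the mixed population.

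**The concern.** The population analysed and the population named in the question differ. The pooling argument is about antimicrobial regimens, but the primary outcome is length of stay. Nothing in the article says that the two diagnoses share a discharge hazard, or that the audit-and-feedback intervention (ASP-i) changes it equally in both. Drawing on two guidelines leaves room for the effects to differ.

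Two things are at stake. The first is interpretation: a single pooled HR reported as the CAP effect is a mixture whose weights are not known. The second is comparability. The study is not randomised, and a patient becomes exposed only if still in hospital at 48 hours or later and meeting the review criteria. If diagnosis affects who is reviewed and when, exposed and unexposed patient-time can differ in diagnosis, and the listed covariates do not adjust for it directly.

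**Working it through.** **Inputs from the article.** 400 to 500 patients a year for 24 months, so N = 800 to 1,000; 70% discharged alive; two-sided alpha 0.05; power 0.8 (Sample size section).

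**Inputs assumed.** Half of the patients exposed; COPD-exacerbation share f of 20 to 40%; the diagnosis-specific HRs used below. None of these is in the article.

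**1. The plan's own figure.** With D = 0.70 × N events, the detectable HR is exp(2.8016 / √(D × 0.25)), and the reduction in stay is taken as 1 − 1/HR.

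| N | Events | Detectable HR | Reduction |
|---|---|---|---|
| 800 | 560 | 1.267 | 21.1% |
| 900 | 630 | 1.250 | 20.0% |
| 1,000 | 700 | 1.236 | 19.1% |

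This reproduces the stated reduction of about 20%. With 70% exposed, the range is 20.6 to 22.8%. The figure does not depend on the diagnosis question, except that the article does not say whether the yearly count includes COPD exacerbations.

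**2. What pooling could do to the HR.** Approximate the pooled HR by exp[(1 − f) ln HR(pneumonia) + f ln HR(COPD)], and power by Φ(√(630 × 0.25) × ln HR − 1.96). Take HR 1.25 in pneumonia and 1.0 in COPD exacerbation:

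| f | Pooled HR | Power, 630 events |
|---|---|---|
| 20% | 1.20 | 61% |
| 30% | 1.17 | 50% |
| 40% | 1.14 | 39% |

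Now take 1.10 in pneumonia and 1.35 in COPD exacerbation, with f = 30%: exp(0.7 × 0.0953 + 0.3 × 0.3001) = exp(0.1567) = 1.17. The pooled HR is the same although the pneumonia effect is very different. If both HRs are 1.25, the pooled HR is 1.25 at any share and power stays at 80%.

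**3. What a pneumonia-only estimate costs.** Assume that the yearly count includes COPD exacerbations and take N = 900. Events in pneumonia are 630 × (1 − f), that is 504, 441 or 378 for f of 20, 30 or 40%. The detectable HR becomes 1.28, 1.31 or 1.33, against 1.25 pooled. At f = 30% and a true HR of 1.25, power is Φ(√(441 × 0.25) × 0.2231 − 1.96) = Φ(0.38), about 65% against 80%. If the yearly count is CAP alone, this loss does not arise.

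**4. Season.** With three baseline months and then one ward every two months, the four wards contribute 3 + 5 + 7 + 9 = 24 ward-months before rollout, out of 4 × 24 = 96. Of these, 3 + 5 + 7 + 7 = 22 fall in April to October 2013 and none in January to March. Ward-level control time is therefore seasonally unbalanced. But the model contains quarter and ward, and a patient counts as unexposed until the ASP-i is given, so unexposed patient-time accrues through both winters. What remains open is a difference in diagnosis between exposed and unexposed patient-time within the same ward and quarter.

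**The case against.** The wider definition is declared openly and given a reason, the choice of guidelines matches it, and every patient must screen positive for febrile respiratory illness. On this view the short label CAP merely abbreviates a stated operational definition, and pooling is a defensible pragmatic choice. That defends the enrolment, and it rules out the inference that the trial fails to answer its question: a pooled HR still informs the CAP question. It does not defend reporting the pooled HR as the CAP effect.

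A reader might also infer that no pneumonia-only analysis is planned. The article supports only the statement that none is named there, because a subgroup or sensitivity analysis may stand in an analysis plan that is not shown.

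A reader might further infer that winter case mix confounds the result. The quarter and ward terms absorb average seasonal and ward differences, and ward allocation is said to depend only on bed availability. Seasonal bias is therefore not shown.

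Finally, the COPD share and the diagnosis-specific effects are assumed, and the loss of power requires little or no effect in COPD exacerbation, which nothing in the article suggests. That objection stands in full. There is also no gold-standard test for CAP, as the Background says, so any split rests on a clinical label.

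**Conclusion.** The point holds in a limited form. As written, the primary HR is for pneumonia or COPD exacerbation, while the question, recruitment statement and expected conclusions are for CAP. The model as named neither adjusts for nor separates the two diagnoses. Diagnosis imbalance within ward and quarter is possible, because exposure is switched on patient by patient, but the article gives no evidence that it occurs or in which direction it would act.

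The size cannot be fixed from the article. The pooled HRs of 1.20 to 1.14 and the powers of 61 to 39% illustrate one scenario and are not estimates. The firmer conclusion is qualitative: unless the two effects are assumed equal, a single pooled HR cannot identify the effect in pneumonia. A change should be made, since it is specific and cheap.

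**What to change.** Keep the enrolment as it is. Then:

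- Add admission diagnosis (pneumonia versus COPD exacerbation) to the Cox model, as a stratum of the baseline hazard or as a covariate, with a stated rule for patients who have both.
- Report the ASP-i HR in the pneumonia group as a prespecified secondary or sensitivity estimate beside the pooled primary HR.
- Word the question and any conclusion from the pooled HR as applying to pneumonia or COPD exacerbation, and say whether the yearly count in the Sample size section includes both.

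The cost is mainly wording and one variable. The admitting diagnosis is already needed for eligibility, but the article does not say that the two diagnoses are recorded separately, so this must be confirmed. The pneumonia-only estimate is less precise (detectable HR about 1.28 to 1.33 instead of 1.25 under the assumptions above), and the diagnosis label is clinical, so some misclassification between the groups must be accepted.

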### Intervention

All eligible patients with CAP who meet the ASP review criteria will receive the ASP intervention (ASP-i). This intervention consists of a prospective chart audit and physician feedback (persuasive) approach [25]. The ASP members who conduct all the audits and make recommendations consist of a pharmacist trained in infectious diseases (LM) and a physician trained in infectious diseases (GD). All patients are reviewed by both members. The ASP-i recommendations are guided by the Infectious Diseases Society of America CAP guidelines [1] and the Canadian Thoracic Society guidelines for the management of chronic obstructive pulmonary disease [26]. The possible ASP-i recommendations are based on those recommended by the UK National Health Service [25] and include:No change to current careDiscontinue antibioticsIntravenous to oral conversionDuration of therapyDosing changeNarrow or broaden spectrum of therapy.

The ASP-i recommendations are not mutually exclusive. All recommendations are documented in the patient’s electronic medical record and communicated directly to the attending physician by the ASP members.

### Study design

This is a pragmatic controlled non-randomized clinical study intended to measure the effectiveness of a ‘real-world’ program [27]. The ASP-i will be implemented in a modified stepped-wedge design [28]. Baseline patient data will be collected for all enrolled patients on each of the medical wards for the first 3 months of the study, and then the ASP-i will be introduced to each medical ward in a non-randomized sequential fashion in 2-month intervals until all medical wards are exposed to the intervention. This design was chosen for several reasons; the preponderance of evidence suggests that antimicrobial stewardship interventions are beneficial to patient safety and quality of care [29]; there are human resource limitations in rolling out the program simultaneously to all wards; and the design has the advantage of a contemporaneous control group for comparison. The unit of randomization in this study could have been the four medical wards; however, randomization of the wards was not included in the design. The allocation of CAP patients to one of the four medical wards is controlled by bed allocation, an administrative branch of the hospital. Bed allocation was blinded to the study and the process of patient allocation is solely dependent on bed availability. In addition, the patients, regardless of their ward location, were all admitted to the hospitalist service. The hospitalist service provides coverage across all four medical wards and has no influence on the allocation of patients to any of the wards. In essence, the patients will be ‘naturally’ allocated to one of the four medical wards and one of the attending hospitalists by a bed allocation process that is blinded to the intervention, so that the additional randomization of the wards themselves should provide very little benefit with respect to minimizing selection bias. In addition, the four medical wards can all accommodate patients with CAP; however, one of the medical wards has historically accommodated more CAP patients than the other three. As a result, this ward was chosen as the first ward to receive the ASP-I, as this would ensure that the maximum number of CAP patients would have earlier access to the ASP-i. The ethical principle of utilitarianism was used to guide the order of ward exposure to the ASP-i. The target of the intervention is the most attending physician (hospitalist) , while the unit of analysis will be individual patient outcomes adjusted for potential clustering effects within hospital wards.

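### The plan adjusts for clustering by ward only, although the ASP-i targets hospitalists who work across all wards; the interval is too narrow if hospitalists differ in response

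*Protocol article*

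**What the plan says.** Protocol article, Study design: "The target of the intervention is the most attending physician (hospitalist"). The same sentence goes on to take each patient's outcome as the unit of analysis, "adjusted for potential clustering effects within hospital wards".

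Setting: "Hospitalists are not assigned to any one specific medical ward, but provide care across all medical wards". Study design repeats that the hospitalist service covers all four wards.

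Statistical methods lists the final model:
- ASP-i as a time-varying 0/1 covariate;
- the patient covariates "age, sex, Charlson comorbidity index, CURB-65 score, time (days) to clinical resolution, and complications from pneumonia, such as empyema";
- ward, entered "by including them as indicator variables in the final model";
- calendar time ("time variable will be defined as ‘quarter’ from start of study");
- an interaction with acceptance or rejection of the recommendation, for a per-protocol analysis.

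No hospitalist indicator, frailty or clustered variance appears. The Discussion treats cross-coverage by hospitalists only as a source of contamination, to be examined with a time-series test of monthly consult rates.

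**The concern.** The intervention acts through the hospitalist, who receives each recommendation and decides whether to follow it. Patients of one hospitalist therefore share both a discharge habit and a response to the ASP-i. Ward and hospitalist are crossed, so ward indicators absorb little of either.

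Two things are at stake for the primary hazard ratio (HR). First, if the ASP-i works better with some hospitalists than with others, the estimate depends on which hospitalists happened to be on service. A model that treats patients as independent, given ward and quarter, leaves that source of variation out of the standard error. Second, the modelled exposure is actual receipt of the ASP-i. If receipt is more common under hospitalists who discharge slowly (or quickly), the HR picks up part of that difference.

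**Working it through.** **The plan's own figure.** Sample size gives 400 to 500 patients a year for 24 months, 70% discharged alive in the control arm, power 0.80 and two-sided α 0.05. Take N = 900, the midpoint of 800 to 1000, and assume a 1:1 exposure split, which is not stated. Events D = 0.70 × 900 = 630. The Schoenfeld formula gives

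detectable HR = exp[−(1.960 + 0.842)/√(630 × 0.25)] = exp(−0.223) = 0.80.

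N = 800 and N = 1000 give 0.789 and 0.809. The stated effect of about 20% is thus reproduced for independent patients, with no allowance for hospitalists.

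**Assumed inputs.** The protocol gives no number of hospitalists, no between-hospitalist variance and no link between receipt and discharge speed. All of these are assumed below.

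**Simulation A: differences in baseline or in response.** 900 patients, four wards starting at months 3, 5, 7 and 9, ASP-i 2 to 4 days after admission, 14-day censoring, ward and quarter indicators, true average log HR zero, 600 runs per setting. A constant-hazard model was used in place of Cox. Monte Carlo error at 5% is √(0.05 × 0.95/600) = 0.9 points.

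| Hospitalists | SD of baseline log hazard | SD of response (log HR) | True SD of estimate | Model SE | Type I error |
|---|---|---|---|---|---|
| 10 | 0.2 | 0 | 0.088 | 0.091 | 4.5% |
| 10 | 0.3 | 0 | 0.093 | 0.091 | 6.7% |
| 20 | 0.2 | 0 | 0.093 | 0.091 | 6.2% |
| 20 | 0.3 | 0 | 0.091 | 0.091 | 5.3% |
| 10 | 0.2 | 0.15 | 0.109 | 0.091 | 9.7% |
| 20 | 0.2 | 0.15 | 0.102 | 0.091 | 6.8% |
| 10 | 0.2 | 0.30 | 0.129 | 0.091 | 17.8% |
| 10 | 0.3 | 0.30 | 0.129 | 0.091 | 17.8% |
| 20 | 0.2 | 0.30 | 0.116 | 0.091 | 12.3% |
| 20 | 0.3 | 0.30 | 0.110 | 0.091 | 11.0% |

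**Hand check of the response rows.** With K hospitalists whose log HRs have SD τ, the estimate gains variance of about τ²/K. The true SD is then √(0.091² + τ²/K), and type I error is 2 × [1 − Φ(1.96 × 0.091/true SD)].
- τ = 0.15, K = 20: √(0.00828 + 0.00113) = 0.097, giving 6.6%.
- τ = 0.30, K = 10: √(0.00828 + 0.00900) = 0.131, giving 17.5%.

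This agrees with the simulated 7 to 18%. From the simulated SDs, a correct interval would be 0.102/0.091 = 1.12 to 0.129/0.091 = 1.42 times as wide as the planned one.

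**Do hospitalist indicators repair it?** Not when response varies. Adding them in the same runs gave 8 to 21% rejection, because they shift only the baseline hazard.

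**Simulation B: receipt related to discharge speed.** A Cox model with 900 patients, 15 to 25 hospitalists, baseline log-hazard SD 0.3, receipt varying by hospitalist (logit SD 0.7) and 120 runs per scenario. With a correlation of −0.5 or +0.5 between discharge speed and receipt, the null HR averaged 0.95 or 1.05. On the log scale 0.95 is −0.051, about half the SE of 0.103. Hospitalist indicators brought the HR back to 0.98 to 1.02. Rejection was about 10% under the planned model and 6 to 8% with indicators. At 120 runs the Monte Carlo error near 10% is √(0.1 × 0.9/120) = 2.7 points, so that contrast should not be relied on. With hospitalist effects unrelated to receipt, rejection was 4 to 7%.

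**The case against.** Several counter-arguments have force.

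*Nothing about the size comes from the protocol.* This is correct. Harm needs either varying response or a link between discharge speed and receipt, and the protocol documents neither. With baseline differences alone the planned analysis does acceptably.

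*Bed allocation is blinded and driven by bed availability, so hospitalists should be balanced.* This covers which ward and hospitalist a patient gets. It does not cover receipt, which depends on meeting ASP review criteria that the article does not spell out. A link between receipt and hospitalist is therefore possible but not shown, so precision is the main concern and bias the lesser one.

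*Interest may lie only in the hospitalists at this hospital.* The error rates above treat hospitalists as a sample from a wider group. For the average effect among these particular hospitalists, the planned interval is less at fault. The article, however, offers the trial as evidence of effectiveness and as a model for broader use.

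*An article condenses the full plan.* True in general, but here the clustering level is stated and the final model is itemised. It is a stated choice, not an omitted detail.

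A reader might go further and apply the usual cluster-trial design effect, 1 + (m − 1) × ICC. With 10 to 30 hospitalists and an ICC of 0.01 to 0.05 it runs from 1.29 to 5.45, with power at HR 0.80 falling to between 69% and 22%. That is not supported. It assumes each hospitalist treats patients in one condition only, whereas here hospitalists treat both ASP-i and control patients, and stable differences largely cancel. Nor do the documents support saying that the HR is confounded or that the interval is always too narrow.

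**Conclusion.** The point holds in conditional form. The plan sets its clustering adjustment at a level other than the one at which it says the intervention acts, and ward indicators cannot make up the difference.

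- **Hospitalists differ in response to the ASP-i** (assumed log-HR SD 0.15 to 0.30, 10 to 20 hospitalists): the interval is too narrow and type I error is about 7 to 18%.
- **Discharge speed is related to receipt** (assumed correlation ±0.5): a modest bias in either direction, with a null HR of about 0.95 to 1.05.
- **Baseline discharge rates differ, unrelated to receipt:** little harm, with type I error about 4 to 7%.

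Which case applies cannot be told from the protocol. Varying response is plausible, since each attending physician decides whether to act on the recommendation. The change is worth making because it concerns the primary estimate and is purely analytic. The omission does not invalidate the design.

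**What to change.** 1. Obtain the attending hospitalist for every patient from the medical record. For ASP-i patients, use the one who received the recommendation. For the others, fix a rule in advance, for example the attending at 48 hours (the earliest time for an ASP-i under Participant timeline), or at discharge if earlier.
2. Keep the ward and quarter indicators. Add to the final Cox model either a hospitalist frailty with a random ASP-i effect, or a hospitalist-clustered variance with small-sample correction. Hospitalist indicators or a simple shared frailty are not enough, because they shift only the baseline hazard.
3. The clustered variance corrects the interval and leaves the HR unchanged. If it is chosen, report a supporting analysis with hospitalist indicators, to show whether the HR moves.
4. In Study design, extend the phrase "adjusted for potential clustering effects within hospital wards" so that it names attending hospitalists as well as wards, and amend Statistical methods to match.

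Cost: one extra field to abstract if it is not already held (the article does not list it among the collected data), and a somewhat wider interval. The remedy in step 2 was not itself simulated here. Its behaviour with the actual number of hospitalists should be checked before the analysis is fixed.
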